## Abstract

**Background:**

Physical activity (PA) is positively associated with quality of life. People with a stoma are less likely to engage in PA than those without a stoma.

**Methods:**

In this feasibility intervention study, we will perform the following: (1) Develop a PA intervention for people with a stoma. An Expert Working Group of behavioural scientists, exercise scientists, clinicians and a Patient Advisory Group of people with a bowel stoma will meet with the research team to inform the development of a PA intervention for people with a stoma. A manual of the intervention will be the main output. (2) Explore PA instructors’ experiences of delivering the PA intervention. PA instructors will record on paper the number of PA consultations with each patient and a researcher will interview the PA instructors about their experiences of delivering the intervention. (3) Assess the level of patient (bowel cancer or inflammatory bowel disease (IBD) patients with a stoma between 6 weeks and 24 months post-surgery) engagement with the PA intervention and their views on intervention acceptability and usefulness. Patients will keep a PA diary to record daily pedometer recorded step count and type and duration of activities. A researcher will interview patients about their experiences of the PA intervention. (4) Assess screening, eligibility, consent, data completion, loss to follow up, and missing data rates, representativeness of participants and potential treatment effects. A researcher will record on paper all study procedure parameters. Quality of life (stoma-quality of life; Functional Assessment of Cancer Therapy, Short IBD questionnaire), fatigue (FACIT fatigue scale) and PA (accelerometer) will be measured pre- and post-intervention in patients. For IBD patients only, blood will be taken to measure systemic inflammation.

**Discussion:**

We hypothesise that a PA intervention will be an effective means of improving the quality of life of people with a stoma. Before embarking on a full randomised controlled trial to test this hypothesis, a PA intervention needs to be developed and a feasibility study of the proposed PA intervention conducted.

**Trial registration:**

ISRCTN58613962, Protocol version: 0.1. 14 September 2017.

## Background

This article presents a research protocol for a feasibility study of a physical activity (PA) intervention to improve the quality of life in patients with a bowel stoma. The Standard Protocol Items: Recommendations for Interventional Trials (SPIRIT) checklist for reporting intervention trial protocols has been used for guidance [1].

A stoma is an artificial opening on the surface of the abdomen that has been surgically created in order to divert the flow of faeces or urine [2]. The two types of eliminating bowel stomas are colostomy and ileostomy, which can be temporary or permanent [2]. In Europe, approximately 700,000 people are living with a stoma, and in the USA, more than 1 million people have a stoma [3]. It is estimated that there are 100,000 people with stomas in the UK [4]. There are a number of conditions that may necessitate the formation of a bowel stoma including bowel cancer and inflammatory bowel disease (IBD) [2]. Recent systematic reviews suggest that a stoma has a negative impact on quality of life [5–7]. Research about lived experiences and psychosocial health following stoma formation highlights three key themes: psychosocial impact around feeling of loss of control of body function, physical aspects that affect psychological function and quality of life and the process of acceptance, adaptation and adjustment [8]. A systematic review of 11 qualitative studies about people’s experiences of bodily change following stoma formation suggests that people experience profound disruptions in how their body looks, functions, sounds, smells and feels [9]. Interventions are therefore needed that have the potential to improve the quality of life for this group of patients.

PA has been identified by patients with a stoma as a research priority in relation to their quality of life [10]. A recent systematic review found that PA was positively associated with quality of life in long-term (≥ 5 years post diagnosis) bowel cancer survivors [11]. Additionally, emerging evidence suggests an association between PA and quality of life in people with IBD [12]. Yet, in bowel cancer survivors, those with a stoma are less likely to engage in PA than those without a stoma (odds ratio (OR) = 1.51, 95% confidence interval (CI) = 1.12–2.04) [13]. Furthermore, two recent surveys found that people with a stoma report reductions in PA following stoma formation [14, 15]. To address low levels of PA, there is a need to develop PA interventions specifically for people with a stoma.

## Methods

### Aim

We hypothesise that a PA intervention will be an effective means of improving the quality of life of people with a stoma. Before embarking on a full randomised controlled trial to test this hypothesis, a PA intervention needs to be developed and a feasibility study of the proposed PA intervention conducted. The main focus of this study is feasibility and acceptability of intervention implementation and study procedures for recruitment and measures of treatment effects. The objectives of this feasibility study, therefore, are as follows: (1) to develop a PA intervention for people with a stoma; (2) to explore PA instructors’ experiences of delivering the PA intervention; (3) to assess the level of patient engagement with the PA intervention and their views on intervention acceptability and usefulness; and (4) to assess screening, eligibility, consent, data completion, loss to follow up, missing data rates, representativeness of participants and potential treatment effects.

### Design

The research will draw on Stage I Development and Stage II Feasibility and Piloting of the Medical Research Council framework for the development of complex interventions [16]. Stage 1 involves intervention development. In Stage 2, the feasibility and acceptability of the intervention and trial procedures will be assessed using a quasi-experimental design, which will include measures of potential treatment effects being taken pre- and post-intervention.

### Stage 1: Intervention development

The research team already have an idea of what the intervention will look like, which is based on their previous work with cancer patients, including people with bowel cancer [17, 18]. Nonetheless, an Expert Working Group of behavioural scientists, exercise scientists, clinicians and a Patient Advisory Group of people with a bowel stoma will meet with the research team to inform the development of a PA intervention for people with a stoma. A manual of the intervention will be the main output from Stage 1.

The plan is to develop an intervention so that people with a bowel stoma are referred to a PA instructor, trained by the research team, to prescribe and support people with stoma engage in PA. Participants will undergo a physical function and fitness test (6-min walk [19], 30-s sit-to-stand test and chair sit-and-reach and arm-curl test [20]), be offered weekly PA consultations for 12 weeks and receive a pedometer to monitor their weekly PA in a diary designed for the purposes of the study. The PA consultations will be individual, face-to-face or by video conference once a week for 12 weeks. To promote and sustain behaviour change, consultations will incorporate core behaviour change techniques (e.g. goal-setting) recommended by the National Institute for Health and Care Excellence [21].

### Stage 2: Feasibility study

#### Setting

Participants will be recruited from three National Health Service Trusts/Boards: NHS Highland (Scotland); London North West Healthcare Trust; University College London Hospitals NHS Foundation Trust.

#### Eligibility criteria

##### Inclusion

Diagnosed with Stage I–IV bowel cancer OR diagnosed with IBD;> 6 weeks and < 24 months since stoma formation (permanent or temporary) surgery (laparoscopic or open surgical procedure); andWilling and able to provide written informed consent.

##### Exclusion

Emergency surgery for stoma formation;Clinician recommends that the patient should not engage in any type of PA; andOngoing adjuvant therapy (chemotherapy or radiotherapy).

#### Main outcomes of the feasibility study

The main focus of this study is feasibility and acceptability of intervention implementation and study procedures for recruitment and measurement of treatment outcomes.

##### Assessing feasibility and acceptability of intervention implementation

The intervention will involve participants having 12 consultations with a PA instructor. Intervention fidelity will be measured by the number of consultations completed. PA instructors will record for each participant the number of PA consultations, duration and type (e.g. face-to-face, video call, telephone call). The PA instructor will prescribe three types of physical activity during each PA consultation for each week: physical fitness/aerobic activities (e.g. walking, cycling, swimming), muscular strengthening activities and mobility and movement activities. The PA instructor will recommend level of exertion for each type of activity using the Borg RPE Scale [22].

Intervention adherence will be measured as the completion rate of the prescribed PA. The participant will write down the three types of prescribed weekly activities in a PA diary that they will complete for the 12-week duration. Participants will record for each day their daily step count from the pedometer. They will record how much of the prescribed activity they managed that week using a continuous rating scale: all of it (100%), most of it (75%), some of it (25%), and none of it (0%). Hence, intervention adherence will be measured by the average completion rate of the three different types of prescribed activities. They will describe any additional physical activities they did during the week, how they felt doing the prescribed activities (e.g. challenges) and if they had any issues with their stoma.

The acceptability of the intervention will be explored through semi-structured face-to-face or telephone interviews (depending on participant preference) with participants and PA instructors. A semi-structured interview is chosen as it allows flexibility with sequencing of questions and for following up on any topics that arise naturally through discussion [23]. These interviews will last approximately 30 min and cover participants’ and PA instructors’ opinions on perceived stoma-related barriers to PA, content of the PA intervention and its perceived relevance and usefulness in addressing stoma-related barriers to being physically active.

##### Assessing study procedures

Screening, eligibility, consent and data completion and loss to follow up rates and reasons for excluding patients will be presented as percentages. Recruitment rates will be measured as rate of invited participants who are eligible and consenting. Clinical information including diagnosis (e.g. cancer or IBD), surgery (e.g. open or laparoscopy), date of stoma surgery, disease staging, stoma type (e.g. permanent or temporary, ileostomy or colostomy) and demographic information (e.g. age, sex) will be collected to assess representativeness of participants. Suitability of measurement procedures will be evaluated based on completion rates and rates of missing data.

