#### Sample size

It is inappropriate to base feasibility study sample sizes on measures of intervention effect, which is the purpose of the full-scale trial. Although how many participants are required in a feasibility study remains equivocal, suggestions range from 10 to 75 [32]. We aim to recruit 30 participants across three sites which should provide a sample of participants with different demographic and clinical characteristics that will improve our confidence in the conclusions we draw from this feasibility study.

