#### Data analysis

Quantitative data analysis will be conducted in three steps. First, descriptive statistics will be used to describe demographic and clinical characteristics of the studied population stratified by eligible consenting and non-consenting participants, and screening, eligibility, consent and data completion rates and reasons for excluding patients reported as percentages. Second, intervention fidelity and intervention adherence continuous data (e.g. number of PA consultations, pedometer step count) will be presented as means and standard deviation and categorical data (type of consultation) as percentages. Third, assuming continuous data outcomes, differences pre- and post-intervention will be presented by the mean difference with the associated 95% confidence interval following *t* test analysis. This is because the focus of the results from this feasibility study will be on the estimates of treatment effects rather than statistical significant and hypothesis testing, which is the purpose of a full trial. Qualitative thematic analyses of audio-recorded interviews will be conducted using the Framework approach which is a rigorous method providing a structure within which qualitative data are organised and coded and themes identified [33].

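### Procedural feasibility rates, part of the main outcomes, are planned as percentages without intervals, while 95% confidence intervals go only to the pre-post changes classed as other outcomes

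*Protocol article*

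**What the plan says.** *Main outcomes of the feasibility study* sets the priority: "The main focus of this study is feasibility and acceptability of intervention implementation and study procedures for recruitment and measurement of treatment outcomes". For the procedural part, *Assessing study procedures* fixes the summary: screening, eligibility, consent, completion and "loss to follow up rates and reasons for excluding patients will be presented as percentages". The same section defines the recruitment rate on those invited, and judges whether the measures are suitable from completion and missing-data rates, with no level given.

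*Data analysis* has three steps. Step one repeats percentages for screening, eligibility, consent and completion. Step two gives means and standard deviations for fidelity and adherence, and percentages for consultation type. Step three covers the pre-post differences, which "will be presented by the mean difference with the associated 95% confidence interval". These differences belong to *Other outcomes of the feasibility study*. The article explains the interval by saying that the results are about estimating treatment effects and not about testing.

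*Sample size* declines an effect-based calculation ("It is inappropriate to base feasibility study sample sizes on measures of intervention effect, which is the purpose of the full-scale trial"), cites a suggested range of 10 to 75, and continues: "We aim to recruit 30 participants across three sites which should provide a sample of participants with different demographic and clinical characteristics". It adds that this "will improve our confidence in the conclusions we draw from this feasibility study". No precision is stated for any outcome.

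**The concern.** The article chooses a summary for each class of outcome, and the choice does not match its own priorities. Its argument for estimation over testing applies at least as well to consent, retention and completion, yet only the secondary pre-post changes receive an interval.

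These rates matter because the study is preparatory to a full randomised trial. *Discussion and dissemination* says that it will not indicate the future sample size and will not test whether randomisation is acceptable. It also notes that trials which follow feasibility work often fail through poor recruitment, and that sites vary widely. Recruitment, retention and completion are therefore among the main quantitative results that the study can hand on. A retention percentage quoted without its interval invites the next team to plan on it as if it were known.

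**Working it through.** **No figure to reproduce.** The article gives no power, precision target or threshold behind 30. The number lies inside the cited range of 10 to 75, and nothing more can be checked. What can be worked out is the precision that 30 delivers.

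**Inputs.** n = 30, from *Sample size*. Observed rates of 50% to 90% are assumptions, as are the numbers invited used below; the article gives neither.

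**Rates with denominator 30 (retention, completion).** The exact (Clopper-Pearson) limits for x out of n are the 2.5% quantile of Beta(x, n − x + 1) and the 97.5% quantile of Beta(x + 1, n − x). The normal half-width is 1.96 × √(p(1 − p)/30).

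| Observed (assumed) | Exact 95% interval | Normal half-width |
|---|---|---|
| 15/30 = 50% | 31.3% to 68.7% | 17.9 points |
| 18/30 = 60% | 40.6% to 77.3% | 17.5 points |
| 21/30 = 70% | 50.6% to 85.3% | 16.4 points |
| 24/30 = 80% | 61.4% to 92.3% | 14.3 points |
| 27/30 = 90% | 73.5% to 97.9% | 10.7 points |

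For example, at 80%: 1.96 × √(0.8 × 0.2/30) = 0.143. Over rates of 50% to 90% the half-width is about 11 to 18 points. Exact intervals are a little wider and not symmetric: at 27/30 the lower limit is 16.5 points below the estimate and the upper limit 7.9 above. Wilson intervals are slightly narrower, for example 62.7% to 90.5% at 24/30.

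**Rates with another denominator (consent, recruitment).** With 30 consenting, the exact interval depends on the assumed number invited: 30/40 = 75% (58.8% to 87.3%); 30/60 = 50% (36.8% to 63.2%); 30/100 = 30% (21.2% to 40.0%); 30/300 = 10% (6.8% to 14.0%). The precision for n = 30 must not be carried over to these rates.

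**Mean fidelity and adherence.** The 95% half-width is t(0.975, 29) × SD/√30 = 0.37 SD if all 30 contribute data.

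**Is 30 itself the problem?** Exact binomial probabilities for a rule fixed in advance, with cut-offs chosen only for illustration:

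| Call it feasible if | Probability if the true rate is low | Probability if the true rate is high |
|---|---|---|
| at least 26 of 30 | 0.030 at 70% | 0.82 at 90% |
| at least 20 of 30 | 0.049 at 50% | 0.89 at 75% |
| at least 23 of 30 | 0.044 at 60% | 0.76 at 80% |

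Thirty participants can separate rates some 20 to 25 points apart with reasonable reliability.

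**The case against.** The strongest reply is that this is a condensed article. Intervals around descriptive percentages, and numerical progression criteria, may sit in the full protocol or analysis plan; presenting a percentage does not rule out an interval; and a reader given the counts can compute one. That stands for progression criteria: their absence here does not show that none exist. It has less force for the intervals, because the article does specify the summary for each outcome class and names an interval for only one of them.

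Three stronger readings are tempting, and the document does not support them.

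- A reader might infer that every main outcome is a bare percentage. Fidelity and adherence are means with standard deviations, from which an interval follows once n is known, and acceptability is explored by interview.
- A reader might infer that 30 patients cannot support a conclusion. The calculation above shows otherwise when a rule is set in advance. The article also announces no formal go/no-go decision: it says that the study will inform a full trial, and it plans an internal pilot at all sites of that trial.
- A reader might take the *Sample size* remark about confidence as a claim of statistical precision. In context it is about the diversity of participants, so it is not wrong for lacking a precision figure. Adding one would still help.

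**Conclusion.** The point holds in a limited form. Rates belonging to the main focus are planned without a measure of uncertainty, and the only intervals go to outcomes of lower rank. For retention and completion with all 30 participants in the denominator, the unreported uncertainty is about 11 to 18 points either side for rates between 50% and 90%; an assumed 80% is compatible with 61% to 92%. The observed rates are assumptions, and missing participants would widen the intervals if the denominator falls. Consent and recruitment rates follow their own denominators, which the article does not give. The defect is in the reporting and not in the number 30. Nothing shown establishes that the judgement of feasibility would be made after seeing the results.

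**What to change.** 1. In *Assessing study procedures* and *Data analysis*, report each procedural rate as a count and percentage with an exact or Wilson 95% confidence interval, and name its denominator (screened, invited, or recruited). List loss to follow-up in *Data analysis* as well. For social media recruitment, where people contact the team themselves, there is no count of those invited, so give the number recruited without a consent rate.
2. Give 95% confidence intervals with the means for fidelity and adherence.
3. In *Sample size*, add that 30 participants give about 11 to 18 percentage points either side, by the normal approximation, for rates of 50% to 90%.
4. If the rates will be used to decide on the full trial, fix the progression criteria before the data are summarised, or state where they are held. The cut-offs are for the study team to choose.

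This needs no extra participants or data: only wording and a few lines of code. Recruitment was still under way when the article was written, so the change could precede the summary of results. The downside is that the reported rates will look less certain.

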#### Other outcomes of the feasibility study

We will assess the feasibility and acceptability of the proposed outcomes for a future randomised controlled trial at baseline and follow-up. We will also estimate potential treatment effects.

##### Quality of life

Stoma-related quality of life (QoL) will be measured using Stoma-QoL [24]. Nineteen items are scored in relation to work/social function, sexuality/body image, stoma function, financial concerns and skin irritation. Overall satisfaction with life is scored from 0 to 100, with a higher score indicating better QoL. To our knowledge, no recommended minimal important differences (MIDs) have been published for this instrument.

Bowel cancer-related QoL will be measured using the Functional Assessment of Cancer Therapy (FACT-C) [25]. The instrument includes general and colorectal cancer-specific subscales. Thirty-seven items are scored in relation to physical, social, emotional and functional well-being, and a specific section for colorectal cancer, and stoma QoL. A higher score indicates better QoL. The recommended MIDs are 2–3 points for the colorectal cancer subscale and 5–8 points for the FACT-C total score [26].

IBD-related QoL will be measured using the Short Inflammatory Bowel Disease Questionnaire (SIBDQ) [27]. The instrument measures physical, social and emotional status, with a higher score indicating better QoL. An evaluation of the Patient-Reported Outcomes Measurement Information System in a large cohort of patients with IBDs recommended MIDs in the range of 2–6 points [28].

##### Fatigue

Fatigue will be measured using the FACIT Fatigue Scale, which is a short, 13-item questionnaire that measures an individual’s level of fatigue during their usual daily activities over the past week [29]. The score range is 0–52, with a score of < 30 indicating fatigue. The recommended MIDs are 3 points [30].

##### Physical activity

The amount of PA will be objectively measured using the Actigraph GT3X+ accelerometer (Actigraph LLC, Pensacola, FL, USA) [31]. It will be worn around the wrist and measures activity counts, steps, inclinometers and light and moderate to very vigorous PA. Accelerometers record movement in such a way that it can be translated into a number of different outputs, for example, total step count, bouts of PA at specified intensities or energy expenditure. Accelerometer devices will be initialised by a researcher as follows: (1) Device recording of PA will be set for 7 days, with the intention to gain at least 4 usable days of data for each participant (4 days is standard practice). (2) The date and time when the participant is scheduled to wear the device will be set. The sample rate will be set to 30 Hz. (4) The unique participant ID will be added to the specific device. Once the device is returned by a participant, Actigraph software will be used to download data as follows: (1) the unit of measurement will be set at 10-s epochs; (2) the ‘# of axis’ setting will be set to 3; and ‘steps’, ‘lux’, ‘inclinometer’ and ‘low frequency extension’ will all be selected. Actigraph software wear-time validation will be set to meet the following criteria: (1) minimum number of valid days required = 4, (2) non-wear-time will be set at > 60 min of consecutive zeros and (3) minimum number of wear hours per day required will be set at > 10 h (600 min). Commonly accepted cut-off points for adults will be used to differentiate PA intensity using Freedson et al. [31] adult cut-off criteria: sedentary < 100 counts per minute, light 100–1951 counts per minute, moderate 1952–5724 counts per minute and vigorous > 5725 counts per minute. In addition, a sedentary bout will be set at 10 min.

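### Wrist-worn accelerometer counts, recorded on three axes with the low-frequency extension on, are classified by general adult thresholds with no stated basis for that set-up, so intensity minutes and their change are probably biased

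*Protocol article*

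**What the plan says.** The Physical activity section of the protocol article specifies the measurement closely. On wear site and outputs: "It will be worn around the wrist and measures activity counts, steps, inclinometers", together with activity by intensity. Sampling is at 30 Hz. On download, "the unit of measurement will be set at 10-s epochs", "the ‘# of axis’ setting will be set to 3", and the low-frequency extension is among the options selected ("steps’, ‘lux’, ‘inclinometer’ and ‘low frequency extension’ will all be selected").

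Intensity is then assigned as follows: "Commonly accepted cut-off points for adults will be used to differentiate PA intensity". The bands are sedentary below 100, light 100 to 1951, "moderate 1952–5724 counts per minute", and vigorous above 5725. One published source is cited. The article does not say for which wear site, axis (a single axis or the three-axis magnitude) or filter setting these values were derived, and it mentions no wrist thresholds or wrist correction.

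Under Other outcomes, the measures are described as those proposed for a future randomised trial, and potential treatment effects are to be estimated. Under Data analysis, continuous outcomes are reported as the pre-post mean difference with its 95% confidence interval.

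**The concern.** An activity count is not a physical unit. Its value for a given movement depends on where the device sits, which axis or combination of axes is summed, and which frequency filter is applied. A threshold in counts per minute therefore carries its meaning only under the conditions in which it was calibrated. The article fixes all three conditions and fixes the thresholds, but never connects them.

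There are two reasons to expect an upward error, both from general measurement reasoning and not from the article. A wrist device registers hand and arm movement while the body is still. A filter setting named "low frequency extension" can be expected to admit slower movement and so add counts. Both would move time out of the sedentary band and into the higher bands.

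Physical activity is the behaviour that the intervention targets, and the accelerometer is a candidate outcome for the full trial. If intensity minutes are misclassified here, the estimated change is hard to interpret and the same processing rule may be carried forward.

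**Working it through.** The article gives no ratio of wrist counts to calibration-scale counts and no count distribution. The check below is therefore a sensitivity calculation on stated assumptions.

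**Inputs from the article (Physical activity):** thresholds 100, 1952 and 5725 counts per minute.

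**Assumptions:** recorded counts are k times the counts on the scale for which the thresholds were set, with k constant; a wear day of 14 h = 840 min; minute-level counts are lognormal with median 300 and log-SD 1.3.

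**Step 1: effective threshold.** A recorded count of 1952 corresponds to 1952/k on the calibration scale.
- k = 0.8: 1952/0.8 = 2440
- k = 1: 1952
- k = 1.5: 1952/1.5 = 1301
- k = 2: 1952/2 = 976
- k = 3: 1952/3 = 651

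For k from 1.5 to 3, the effective moderate threshold lies inside the article's own light band (100 to 1951). At k = 3 the vigorous threshold acts like 5725/3 = 1908, below the nominal moderate threshold.

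**Step 2: minutes per day.** Moderate-to-vigorous minutes = 840 × [1 − Φ((ln 1952 − ln(300k))/1.3)]. Sedentary minutes = 840 × Φ((ln 100 − ln(300k))/1.3).

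| k | Moderate-to-vigorous (min) | Sedentary (min) |
|---|---|---|
| 0.8 | 44.9 | 210 |
| 1 | 62.9 | 167 |
| 1.5 | 108.8 | 104 |
| 2 | 153.0 | 71 |
| 3 | 231.6 | 38 |

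The pattern is not peculiar to one distribution. With median 150 and log-SD 1.5, moderate-to-vigorous time goes from 36.6 min at k = 1 to 62.9 at k = 1.5 and 137.7 at k = 3. With median 500 and log-SD 1.3, it goes from 123.8 to 194.0 and 352.6.

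**Step 3: does the error cancel in the pre-post change?** Assume a true 20% rise in the median (300 to 360) with k the same at both visits.

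| k | Pre (min) | Post (min) | Change (min) | Change / pre |
|---|---|---|---|---|
| 1 | 62.9 | 81.3 | 18.4 | 29% |
| 1.5 | 108.8 | 135.6 | 26.8 | 25% |
| 2 | 153.0 | 186.0 | 33.1 | 22% |
| 3 | 231.6 | 272.5 | 40.9 | 18% |

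(Changes were taken before rounding.) The same behavioural change appears as 18 or 41 min/day depending only on k, and the relative change moves the other way. A constant scale error does not cancel once a threshold is applied. Total count volume behaves differently: a constant k multiplies both visits, so the ratio of post to pre is untouched.

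**The case against.** **The origin of the thresholds is not in the article.** A reader who knows accelerometry may infer that these are single-axis, standard-filter values for a device at the waist. The article calls them only commonly accepted for adults, and the cited source is not at hand. This objection stands, so the point is put as a missing link between set-up and thresholds, not as a proven waist calibration.

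**Direction and size are assumed.** A reader might conclude that moderate-to-vigorous activity will certainly be overstated. The documents do not support that: sign and size depend on k, and at k = 0.8 the bias reverses (44.9 against 62.9 min). This also stands. Upward bias is probable, not established, and the range 1.5 to 3 is illustrative.

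**Differential bias through arm exercise.** One might argue that the prescribed strengthening and mobility work uses the arms, so k itself shifts after the intervention. The article names these activity types without a body region, the arm-curl is a fitness test, and it does not say whether prescribed exercise continues in the follow-up wear week. The argument is dropped. The non-cancellation shown above does not need it.

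**The inclinometer.** One might add that its posture output is unsuitable at the wrist. It is only a selected software option, and no posture outcome is planned, so no result depends on it.

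**Little depends on this outcome.** The main outcomes are feasibility and acceptability. Measurement suitability is judged on completion and missing-data rates, which the cut-points for intensity do not affect. Fidelity and adherence use consultation records and diaries with pedometer steps, and the article says that the study will not indicate a sample size for the full trial. This stands and limits the severity.

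**It is a detail for the analysis plan.** This does not stand. The article itself states site, axes, filter, epoch and exact cut-points. The problem lies in how stated choices fit together.

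**Conclusion.** The concern holds in this form. The article pairs wrist wear, three axes and the low-frequency extension with general adult count thresholds and offers no basis for that pairing. Followed as written, it gives sedentary and moderate-to-vigorous minutes, and a pre-post change in them, that cannot be relied on and are probably biased towards too much moderate-to-vigorous activity.

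The size cannot be derived from the documents. If k is 1.5 to 3, the moderate threshold acts like about 1300 to 650. Under the illustrative distribution (median 300, log-SD 1.3), daily moderate-to-vigorous time is then about 1.7 to 3.7 times its correctly scaled value (108.8/62.9 and 231.6/62.9), and an 18-min change reads as 27 to 41 min. These figures rest on the assumed ratio, distribution and wear time. The conclusion that the change is affected rests only on k differing from 1 and on thresholding being non-linear.

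Severity: should-fix. The outcome is secondary, the study has one group with a target of 30 participants, and the main feasibility outcomes do not use it.

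**What to change.** Keep wrist wear, because recruitment is under way and changing site midway would make the data inconsistent. Replace the stated thresholds with an intensity method validated for wrist wear, applied to the 30 Hz recordings with the axis and filter setting of that validation, and name the method and those settings in the protocol. Apply the same processing to the baseline and follow-up files of every participant, including those already recorded.

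Report total count volume and steps alongside. Neither uses the intensity thresholds. Their absolute values are still specific to the wrist and the filter, and the text should say so.

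The cost is a wording change and reprocessing of existing files, with no added burden for participants. This assumes that the 30 Hz files are kept. The Data management section retains all electronic data but does not name these files, so retention should be confirmed. The downside is less direct comparison with studies that used the stated thresholds.
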